## Discussion

Two pilot RCTs helped to establish a protocol for the evaluation of the feasibility and effectiveness of the FindMyApps intervention. Although the protocol for the present study was amended in light of the 2020 coronavirus pandemic, this study goes further than any previous study of the FindMyApps intervention in four important ways.

First, by conducting the effect evaluation in a larger study (n_tot_ = 150; 75 experimental group, 75 control group), we hope to conduct this trial with a reasonable power to detect medium effect sizes (MANCOVA: η^2^ = 0.06; power 0.80, alpha = 0.05), to be able to conduct analyses from which robust conclusions about the intervention’s effectiveness for the target group of community dwelling people living with MCI/dementia and their caregiver can be drawn. A frequent criticism of eHealth or digital health interventions has been a lack of scrutiny in the context of high quality RCTs [11]. This trial will also contribute to the growing pool of RCTs in the field of eHealth and digital health, which is needed for the field to mature.

Second, by means of a process evaluation to review implementation of the FindMyApps intervention among a larger group of participants, we aim to leverage better insight into the contextual, implementation and mechanisms of impact factors that may influence implementation and adoption of FindMyApps, and the study outcomes. This will better inform further evaluation and implementation of FindMyApps compared with existing research.

Third, we aim to extend recruitment for the study from a regional to a national level, to include participants from throughout the Netherlands. With the exception of the three characteristics on which participants are stratified prior to group allocation (diagnosis of MCI or dementia; whether the participant has previously used a tablet or not; and whether or not the caregiver cohabits with the person with dementia), there is no a priori hypothesis regarding subgroups who may derive more benefit from FindMyApps. The trial is therefore designed to be as representative and ecologically valid as is feasible within the scope of a controlled trial. By recruiting people with dementia of different etiologies and with a broad demographic base, the conclusions drawn from this trial will be applicable to a broad group of people with dementia and at a national level. This is important for the planning of large-scale implementation of the FindMyApps intervention if it proves to be effective. Regardless of the main effect and cost-effectiveness analyses, subgroup analyses in the present study may suggest hypotheses relating to effectiveness or cost-effectiveness for specific target groups, which could form the basis of future studies.

Fourth, this trial incorporates for the first time a cost-effectiveness analysis. If a main effect of the FindMyApps intervention is found, we will also be able to conduct an analysis allowing a comparison of the cost-effectiveness of FindMyApps with other interventions targeting similar outcomes in similar target groups and settings. Combined with the effect analyses, this will directly inform decision-making by policy-makers, care funders, care providers and individuals with respect to the implementation of the FindMyApps intervention, and/or other interventions which target similar outcomes. As such, the present study will support the efficient use of limited resources within the care sector in the Netherlands to improve the lives of community-dwelling people with dementia and their caregivers.

Limitations of the research will also be fully discussed alongside the publication of any results. Some limitations are inherent to the design of the study. Most importantly, it is not possible to blind the participants or the researchers administering the intervention to the group assignment. Participation in the study is voluntary and it should also be anticipated that the study population may differ from the general population, with respect to their intrinsic motivation and interest in the use of a tablet. Finally, the dyadic design of the intervention means that the results of the study will not be generalizable to the implementation of the intervention with people with dementia in the absence of input from a formal or informal caregiver.

We aim to widely disseminate the results of this study, to facilitate further improvement of FindMyApps and inform the design and implementation of other tablet-based interventions for the provision of psychosocial care for people with dementia. Through widespread reporting of the results, our goal is to reduce stigma experienced by older users of technology. We expect to provide results that will support efficient and effective decision-making by policymakers, care organizations and individuals with regard to investments in technology for older users of technology, especially those with cognitive impairments. Depending on the outcomes of the effect and cost-effectiveness analyses, we will take action to improve the intervention and/or stimulate further dissemination, if appropriate.

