### Sample size

Two pilot randomized controlled trials preceded this definitive trial, both of comparable design with comparable outcome measures [36, 37]. Values of partial eta squared with respect to primary outcomes measured with instruments which will also be used in the present study, were found to range from 0.01 (MSPP) to 0.38 (PAL). These correspond to small to large effect sizes, respectively, when compared to Cohen’s suggested benchmarks [38]. Previous evaluations of interventions implemented in the Netherlands to improve social health in dementia have also found moderate to large effect sizes, with respect to similar outcome measures [39, 40]. Whilst both pilot studies also revealed small between group differences with respect to a number of outcomes, this trial will not be powered to detect small effects of the intervention. We do not believe that small effects of the intervention – even if statistically significant – would be ‘clinically’ significant. We therefore do not feel that we could justify the additional use of public funds to conduct the trial in such a way as to have adequate power to detect small effects of the intervention.

Effects of the intervention on primary outcomes for the primary participants (social participation and self-management) will be tested using MANCOVA. An a priori power calculation was conducted using the software G*Power, version 3.1, for main effects MANOVA, assuming two dependent variables, two groups, alpha = 0.05 and power = 0.8, and a moderate overall effect. The total required sample size would be *n* = 158. This is an overestimate of the required sample size to achieve a power of 0.8 because the inclusion of covariates in the MANCOVA is expected to increase the statistical power of the test compared to MANOVA (thereby reducing the required sample size for the desired power of 0.8).

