In the two pilot trials evaluating the FindMyApps intervention, drop-out rates were 12 and 37% between baseline and three-month follow-up [36, 37]. Other randomized controlled trials evaluating the effectiveness of technology for social health in dementia that we are aware of, have experienced drop-out rates from baseline to three-month follow-up of around 20% [41, 42]. We are also aware of recently-conducted RCTs involving community-dwelling participants with dementia in the Netherlands, one of which reported a drop-out rate of 12% after three months and the other reported a dropout rate of 35% after six months [39, 43]. A recent review of web-based brain health interventions designed for healthy adult participants identified trials which reported drop-out after various periods of time, with rates ranging from 2 to 52% [44]. With respect to the present study, allowing for a dropout of 20% in the calculation of statistical power for a per protocol analysis, 94 participants per group would have to be randomized. However, this number may be lower in practice if the actual dropout rate is less than 20%. This is a reasonable expectation given that both the FindMyApps intervention and the trial procedure have been improved based on the results from the pilot studies. In the first instance we will therefore aim to randomize 75 participants per group. We will review this target based on the actual drop-out rate as the trial progresses.

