### Allocation

Participants will be randomly assigned to either the FindMyApps (experimental) or usual care (control) arm. Randomization will be performed via Castor EDC, following a variable blocked randomization method, with a target of 1:1 allocation and randomly selected block sizes of 4 or 6. Group allocation will be stratified on the basis of diagnosis (MCI or dementia) and any prior experience with the use of a tablet (participant self-report; ‘Yes’ or ‘No’).

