### Data management and analysis

Quantitative demographic data and data pertaining to participants who withdrew from the study after randomization (dropouts) will be analyzed with descriptive statistics. Differences between the trial arms will be tested with appropriate (non) parametric differences tests (Chi2, Mann-Whitney U, Student’s t-test).

For the effect evaluation, differences between the groups on the primary outcome measures will be tested by MANCOVA on post-test data, including baseline data and potential confounders as covariates in the analysis. Diagnosis (MCI or dementia) will be included as a fixed factor. We will carry out both intention-to-treat and ‘per protocol’ analyses following completion of data collection. Where we encounter missing data as a result of participants withdrawing from the study, we will use appropriate methods to impute that data and perform sensitivity analyses accordingly. Analyses will be conducted using SPSS. We will primarily report effect sizes with calculated 95% confidence intervals, however we will also report *p*-values. We will use 2-tailed p-values with an alpha of 0.05.

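### Power of 0.80 is attached to 150 randomised dyads, but the plan's own calculation needs 158 analysed, and the gap rests on a covariate gain that is never quantified

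*Protocol article*

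**What the plan says.** The protocol article, Sample size, describes a G*Power calculation for a main-effects MANOVA, "assuming two dependent variables, two groups, alpha = 0.05 and power = 0.8, and a moderate overall effect". Its result is: "The total required sample size would be *n* = 158". The section then calls this number an overestimate, because "the inclusion of covariates in the MANCOVA is expected to increase the statistical power of the test compared to MANOVA". It gives no correlation or proportion of variance explained.

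The same section turns to drop-out. It reports 12% and 37% in the two pilots of this intervention and around 20% in comparable trials. The inflated number is given with these words: "a dropout of 20% in the calculation of statistical power for a per protocol analysis, 94 participants per group would have to be randomized". It then argues that drop-out below 20% is a reasonable expectation after improvements since the pilots, and concludes: "In the first instance we will therefore aim to randomize 75 participants per group". The target is to be reviewed against the observed drop-out.

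The Discussion, first point, takes the total of 150 and attaches to it "reasonable power to detect medium effect sizes (MANCOVA: η^2^ = 0.06; power 0.80, alpha = 0.05", with no allowance for drop-out. The Abstract also gives 150 dyads as the trial size.

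**The concern.** The reason given for 75 per group does not lead to 75 per group. Drop-out determines how many must be randomised so that 158 can be analysed. At zero drop-out the answer is 158, and at any positive rate it is more. Only the covariate gain could bring the number below 158. That gain is mentioned once and has no value, and the sentence that sets the target rests on drop-out instead.

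The plan declines to power for small effects, so the moderate-effect claim is the whole basis for interpreting a negative result. The article says the findings will influence national implementation, for or against. A reader who takes 0.80 at face value would treat a null result as a one-in-five chance of missing a moderate effect. At 20% drop-out with no covariate gain, the chance is nearly one in three.

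**Working it through.** **Inputs.** From Sample size: two outcomes, two groups, alpha 0.05, power 0.80, a moderate effect, total 158, and drop-out of 12%, 20% and 37%. From Allocation: equal groups ("with a target of 1:1 allocation"). From Data management and analysis: "We will use 2-tailed p-values with an alpha of 0.05"; the multivariate F test has no direction, so this does not alter it. From Discussion: eta-squared 0.06 and N = 150. Assumption: the moderate effect is f² = 0.0625, which the first step checks.

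**Formula.** For two groups and p = 2 outcomes, the multivariate test is an exact F test with df1 = 2, df2 = N − 3 and noncentrality λ = N × f². Power is the probability that this noncentral F exceeds the 95% point of the central F.

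**Reproducing the plan's figure.** At f² = 0.0625:
- N = 157: λ = 9.81, power 0.7995.
- N = 158: λ = 9.875, power 0.802.

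The smallest N reaching 0.80 is 158, as stated. With eta-squared 0.06, f² = 0.06/0.94 = 0.0638 and the smallest N is 154. In the other direction, f² = 0.0625 is eta-squared 0.0625/1.0625 = 0.0588, which rounds to 0.06. The two sections are therefore using essentially the same effect size.

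**Power with 150 randomised, no covariate gain.**

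| Drop-out | Analysed | f² = 0.0625 | eta-squared 0.06 |
|---|---|---|---|
| 0% | 150 | 0.78 | 0.79 |
| 12% | 150 × 0.88 = 132 | 0.72 | 0.73 |
| 20% | 150 × 0.80 = 120 | 0.68 | 0.69 |
| 37% | 150 × 0.63 = 94.5 | 0.56 | 0.57 |

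**The randomisation target.** 94 per group less 20% is 75.2. So 75 per group is about what would remain after the plan's own 20% loss, yet it is used as the number to randomise. To have 158 analysed after 20% drop-out, 158/0.8 = 197.5, that is 198 in total or 99 per group, would have to be randomised.

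**How much covariate gain is needed.** Suppose the effect is on the unadjusted scale and covariates explain the same share R² of the variance of each outcome. The effect becomes f²/(1 − R²), and df2 falls by the number of covariate terms (four assumed here; this hardly matters). At 120 analysed, power 0.80 needs f² of about 0.0824. Hence R² = 1 − 0.0625/0.0824 ≈ 0.24 and r = √0.24 ≈ 0.49. In the same way, for f² = 0.0625:
- 150 analysed: R² ≈ 0.05, r ≈ 0.22.
- 132 analysed: R² ≈ 0.16, r ≈ 0.41.
- 120 analysed: R² ≈ 0.24, r ≈ 0.49.

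**If 0.06 is already the adjusted effect.** No further gain can be credited. Power at 120 is then 0.69, and 0.80 is reached only at f² ≈ 0.0824, that is eta-squared 0.0824/1.0824 ≈ 0.076.

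**The case against.** The plan's defence is substantial. It calls 158 an overestimate because the planned test is MANCOVA with baseline values as covariates, so the figures without covariate gain describe a weaker test than the one to be run. The correlations needed are not extreme. The article reports test-retest coefficients of 0.71 for the ASCOT and 0.63 to 0.83 by domain for the MSPP. Those are reliabilities, not three-month correlations, which would probably be lower, and none is given for the PAL. Even so, 0.49 is not implausible. The plan also expects drop-out below 20%, sets 75 per group only provisionally, promises a review, and words the Discussion as a hope. With 150 analysed and eta-squared 0.06, power is 0.789 before any adjustment, so the printed figure is optimistic rather than miscalculated.

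All of this stands, and it rules out two stronger readings. A reader might infer that the trial simply has power 0.68. That holds only with 20% drop-out and no covariate gain together, and the plan assumes neither. A reader might also infer from the MANCOVA label in the Discussion that the 0.06 is already adjusted, so that the covariate gain has been spent. The label may only name the test, and Sample size adds the gain on top of the moderate effect. The documents do not settle the question.

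What the defence does not supply is a number. The gain has no stated size, the target is justified by drop-out instead, and the review has no stated trigger or revised target. Nor does imputation in the intention-to-treat analysis by itself recover the information lost with missing outcomes.

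**Conclusion.** The point holds in conditional form. Power 0.80 for 150 randomised dyads is not supported by the plan's own calculation unless a covariate gain of unstated size closes the gap. The argument from lower drop-out fails at every drop-out rate, including zero. Without the gain, power runs from 0.78 to 0.79 (nobody lost) down to 0.68 to 0.69 at the 20% used in the plan's own inflation, and to 0.56 to 0.57 at the worse pilot rate.

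These figures assume a moderate effect of f² = 0.0625 (which reproduces the 158) or eta-squared 0.06, equal groups, and analysis of those who complete follow-up. The correlations of 0.22, 0.41 and 0.49 assume in addition an unadjusted effect and the same R² for both outcomes. Whether 0.80 is attained cannot be decided from the article.

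**What to change.** In Sample size and in the first point of the Discussion, replace the single figure with power for 150 randomised by number analysed, for example at 0%, 12% and 20% drop-out (150, 132 and 120). Give it once without covariate gain (0.78 to 0.79, 0.72 to 0.73, 0.68 to 0.69) and once with a stated and justified baseline to follow-up correlation. Note that about 0.22, 0.41 and 0.49 respectively are needed for 0.80 at f² = 0.0625.

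State whether eta-squared 0.06 is the unadjusted or the covariate-adjusted effect. If adjusted, credit no further gain, and report about 0.69 at 120 analysed, with 0.80 reached only at eta-squared of about 0.076. Remove lower drop-out as the reason for going below 158, and rest the target on the covariate assumption if that is what is meant.

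The cost is wording only. Design, analysis and data collection are untouched, but a printed figure becomes conditional and, without the covariate gain, less favourable.

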## Data Availability

Not applicable.

## Abbreviations

ADQ: Approaches to dementia questionnaire
APH: Amsterdam Public Health Research Institute
ASCOT: Adult social care outcomes toolkit questionnaire
DQoL: Dementia quality of life instrument
EA: Experienced autonomy questionnaire
GDS: Global deterioration scale
MCI: Mild cognitive impairment
MMSE: Mini mental state examination
MRC: Medical Research Council
NPI-Q: Neuropsychiatric inventory questionnaire
PAL: Pleasurable activities list
PES: Positive experience scale
RCT: Randomized controlled trial
SSCQ: Short sense of competence scale
SSI: Semi-structured Interview
TOPICS-MDS: The Older Persons and Informal Caregivers Survey Minimum DataSet
VUmc: Vrije Universiteit Medisch Centrum
